### 8.1.3 Other study parameters (if applicable)

- Demographics: age, sex
- Burn characteristics: Percentage total burned body surface area (TBSA), anatomical affected site(s), date of injury, burn depth determined by an experienced burn physician / plastic surgeon and burn depth determined by a LDI-scan on date 2-5 post burn (prior to the operation), date of surgery
- Clinical characteristics: Fitzpatrick skin type, timing to surgery, number of debridements and/or allograft before autografting, comorbidity, use of tangential excision and/or Versajet techniques, dermatome settings, expansion of skin graft

## 8.2 Randomisation, blinding and treatment allocation

Randomization will be at intra-patient level and performed by means of the Redcap randomization module (most often 5-7 days post allograft application). Preferably 2 wounds in the same patient will be randomized, or alternatively, after discussing this situation with the patient, 1 wound will be divided into 2 halves (A and B). The sequence in which the micrografting and mesh grafting techniques will be applied will also be subject to randomization by means of the Redcap randomization module. In surgical treatment blinding is not possible, as the burn surgeon knows which part of the wound receives what surgical treatment. Outcome assessment will be blinded as the junior investigator/research nurse who does the follow-up measurements is unaware of the technique used in target wound A or B.

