### 4.2 Inclusion criteria

- Patients  $\geq 18$  years
- Clinically deep burn or deep skin defect between 4% and 20% TBSA
- Patients with two comparable deep partial thickness and/or full thickness burns, confirmed by laser Doppler imaging (LDI) or deep skin defects, of minimum 1:2 plissee = 36cm^2, requiring surgery after assessment by a (plastic) surgeon/burn physician
- Patients who are mentally capable to give legal consent or legal representative when the patient is temporarily incompetent (e.g. patient is sedated/ventilated)

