### 4.4 Sample size calculation

Sample size calculation based on scar quality as expressed by POSAS at 12 months post procedure: Paired t-Test for Mean Difference

| Fixed Scenario Elements |        | Computed N Pairs |               |              |         |
|-------------------------|--------|------------------|---------------|--------------|---------|
| Distribution            | Normal |                  |               |              |         |
| Method                  | Exact  |                  |               |              |         |
| Number of Sides         | 2      |                  |               |              |         |
| Alpha                   | 0.05   |                  |               |              |         |
| Mean Difference         | 1      |                  |               |              |         |
| Standard Deviation      | 2.4    |                  |               |              |         |
| Correlation             | 0.5    |                  |               |              |         |
| Null Difference         | 0      |                  |               |              |         |
|                         |        | Index            | Nominal Power | Actual Power | N Pairs |
|                         |        | 1                | 0.8           | 0.807        | 48      |
|                         |        | 2                | 0.9           | 0.902        | 63      |

For a superiority trial comparing 2 paired means, a sample size of 63 patients yields 90% power when assuming a true mean difference of 1, a standard deviation of 2.4 and a moderate correlation of 0.5. Expecting a drop-out rate of 10% the sample size is increased to 70 patients.

Sample size calculation based on donor site size and expansion rate: Paired t Test for Mean Difference

| Fixed Scenario Elements    |           | Computed N Pairs |        |        |       |                     |
|----------------------------|-----------|------------------|--------|--------|-------|---------------------|
| Distribution               | lognormal | Geo              | Geo    | Actual | N     |                     |
| Method                     | Exact     | Index            | Mean 1 | Mean 2 | Power | Pairs               |
| Number of Sides            | 2         |                  |        |        |       |                     |
| Alpha                      | 0.05      |                  |        |        |       |                     |

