## **10. STATISTICAL ANALYSIS**

### **10.1 Primary study parameter(s)**

Scar quality 12 months post-surgery assessed by the observer score of the POSAS scale will be tested for normality before univariate analyses will be performed. If the data are normally distributed, a paired student's t-test will be used for comparison of the data. Otherwise the Wilcoxon signed-rank test will be applied.

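### The order of the two grafting techniques is randomised, but the primary paired test has no order term, which forgoes a small and nearly free gain in efficiency

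*Protocol*

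**What the plan says.** Section 8.2 randomises within the patient, using two wounds or two halves of one wound. It adds a second randomised element: "The sequence in which the micrografting and mesh grafting techniques will be applied will also be subject to randomization".

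Section 10.1 takes the 12-month observer score of the POSAS as the primary variable. If the data are normal, a paired "t-test will be used for comparison of the data"; otherwise the Wilcoxon signed-rank test applies. Neither branch has a term for order or for any covariate.

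The protocol also collects wound depth. Section 8.1.3 lists a clinical assessment and "burn depth determined by a LDI-scan on date 2-5 post burn" among the burn characteristics, without saying that it is recorded separately for wounds A and B. Section 4.2 admits "Patients with two comparable deep partial thickness and/or full thickness burns" and also deep skin defects. Section 10.3 plans only descriptive statistics for the other study parameters.

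Section 4.4 states that "a sample size of 63 patients yields 90% power", "assuming a true mean difference of 1, a standard deviation of 2.4" and "a moderate correlation of 0.5".

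**The concern.** Each patient has one order, so order acts as period does in a crossover trial. If the wound grafted second scores differently at 12 months from the wound grafted first, that shift enters the micrograft-minus-mesh difference with a plus sign in some patients and a minus sign in the others. Pairing removes only what the two wounds share, and order is not shared. A test without an order term counts the shift as random variation.

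What is at stake is some precision in the primary comparison. Section 10.1 names the primary test itself, so this is a choice that the protocol has made and not a detail that it leaves open.

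**Working it through.** **Inputs (section 4.4):** two-sided alpha 0.05, mean difference 1, SD 2.4 per wound, correlation 0.5, 63 pairs.

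**1. The plan's own figure.**
- SD of the difference = √(2 × 2.4² × (1 − 0.5)) = 2.4.
- Noncentrality = √n × 1 / 2.4, with n − 1 degrees of freedom.
- Noncentral t: 48 pairs give 0.807 and 63 pairs give 0.902. Drop-out: 63 / 0.9 = 70.
- All the stated figures reproduce.

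**2. How order enters.** Let o be the effect on the 12-month score of being grafted second instead of first. The within-patient difference is then τ + o in one order and τ − o in the other, where τ is the technique effect. With the orders evenly split, this adds variance o². The protocol gives no value for o, so the values below are assumptions. An order term leaves 61 degrees of freedom.

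| o (assumed) | Share of variance if inside SD 2.4: o²/2.4² | Power with order term | Gain over 0.902 | SD if o comes on top: √(2.4² + o²) | Power of the plain t-test |
|---|---|---|---|---|---|
| 0 | 0 | 0.902 | −0.00015 | 2.40 | 0.902 |
| 0.25 | 1.1% | 0.905 | 0.3 points | 2.41 | 0.899 |
| 0.5 | 4.3% | 0.914 | 1.2 points | 2.45 | 0.890 |
| 1.0 | 17.4% | 0.947 | 4.5 points | 2.60 | 0.852 |

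The two readings are alternatives. If the planning SD already contains the order variance, the order term raises power above 0.902. If the order variance comes on top, the term restores 0.902. For o of 0.25 to 0.5, both readings give about 0.3 to 1.2 points. The last row makes order matter as much as the whole target difference of 1 point, so it is an extreme case.

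**3. Cost.** With no order effect and evenly split orders, power goes from 0.90244 to 0.90229, a loss of 0.00015. This depends on balance, because the standard error of the intercept is 2.4 × 0.5 × √(1/n₁ + 1/n₂). A split of 35 and 28 (assumed for illustration) gives 0.304 instead of 2.4/√63 = 0.302, and power 0.899, which is a loss of about 0.4 points.

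**4. Depth.** A depth effect common to both wounds cancels in the difference. In 4,000 simulated trials of 63 pairs with a patient-level depth effect of 1.5 points and no order effect, the standard error was 0.301 with and without adjustment, and power was 0.91 for both. Only a depth difference between wounds A and B, or a technique effect that varies with depth, could explain variance in the difference. The protocol gives no size for either.

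**The case against.** The strongest reply is that nothing in the analysis is wrong. Technique and order are both randomised, so the paired t-test is unbiased, and its standard error already contains any order variation. The sample size is correct. Every gain rests on an assumed order effect, on a scar scored a year after surgery. Sequence and covariate terms are often settled in a statistical analysis plan, which is not shown here. The Wilcoxon branch has no direct counterpart with an order term.

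Most of this stands and limits the point to efficiency. It does not remove it: section 10.1 commits to a specific primary test that ignores a factor the design randomises, and including that factor costs almost nothing when the orders are balanced.

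Three stronger readings are tempting, and the documents do not support them:

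- **That adjusting for depth would clearly add precision.** Section 4.2 requires comparable wounds and section 8.2 allows two halves of one wound, so much of any depth effect cancels. Section 8.1.3 does not say that depth is held per wound. LDI applies only to burns, while deep skin defects are also eligible.
- **That fewer patients would be needed.** This requires an assumed share of explained variance. At 5%, 10% or 20%, the exact requirement with two added terms is 60, 57 or 51 pairs, but the protocol supports none of these shares.
- **That a mixed model with the 3-month score is the same analysis.** It uses other data and assumes that missing visits are missing at random, so it is a separate option.

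**Conclusion.** The point holds as a modest gain in efficiency that rests on the order term alone. The primary test is valid, and 90.2% power at 63 pairs is correct under the plan's assumptions. A reader might infer that the trial is underpowered or its primary result biased; neither follows.

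With an assumed order effect of 0.25 to 0.5 POSAS points, the test gives up about 0.3 to 1.2 percentage points of power. With no order effect it gives up nothing, and the added term would cost under 0.0002 in power. These figures assume normal differences and nearly even numbers in the two orders. No actual loss of precision has been shown, because the protocol gives no order effect.

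**What to change.** In section 10.1, before any outcome data are examined:

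- Analyse the 12-month within-patient difference in observer POSAS with a linear model whose intercept is the technique effect, with randomised order coded +0.5 or −0.5. Under this coding the order coefficient equals 2o in the notation above.
- Record the order actually applied for each patient. Section 8.1.3 does not list it.
- Add the centred within-pair depth difference only if depth is recorded separately for wounds A and B. State how it is defined for deep skin defects, which have no LDI.
- Keep the paired t-test or Wilcoxon signed-rank test as the sensitivity analysis, so that the non-normal branch stays covered.
- If the 3-month score is also to be used, specify that mixed model separately and state its missing-at-random assumption.

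The cost is a change of wording, one recorded field for order and one degree of freedom (two with depth). It needs no added patients or visits, and the sample size stays as it is.

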**WMO**      **Medical Research Involving Human Subjects Act; in Dutch: Wet Medisch-wetenschappelijk Onderzoek met Mensen**

## SUMMARY

**Rationale:** Deep dermal / sub dermal (burn) wounds need surgical excision followed by skin grafting to achieve rapid wound healing. Most common method is split thickness skin grafting (SSG). However, in extended (burn) wounds there is a lack of donorsite to harvest skin transplants. Moreover, regarding donorsite morbidity it is always high priority to keep donorsite as small as possible. For these reasons, skin grafts are often expanded before application on the wound. Skin graft expansion is generally performed by meshed skin grafting technique, seen this method is considered to be quick and easily applicable. Yet, this technique also has several limitations. For the surgeon this method becomes more cumbersome when the expansion ratio increases. Moreover, the actual expansion of the skin graft is usually lower than the intended expansion ratio and the "fish-net" pattern often stays visible in the eventual scar. An alternative for skin graft expansion is the micrografting technique (Meek technique). In comparison with meshed skin grafting this technique is able to reach true large expansion ratios and thereby maintain small donorsites. As a consequence, this technique is used in particular for very extended (burn) wounds. Both expansion methods are used worldwide in specialized burn centers. Wound healing seems to be similar according to previous published literature. Experience shows a possible advantage of micrografting on scar quality. Three studies compared these two expansion techniques, however none primarily investigated possible differences within long-term scar quality in a prospective study setting. To compare long-term scar quality of micro-versus mesh grafting techniques in deep/subdermal (burn) wounds and thereby providing evidence for the use of micrografting not only for extensive but also for smaller (burn) wounds a randomized controlled trial is highly preferred.

**Objective:** To assess long-term scar quality and donorsite size of deep dermal or sub dermal (burn) wounds after skin grafting with micrografting compared to mesh grafting technique.

**Study design:** Multicenter randomized intra-patient controlled trial.

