## 1. INTRODUCTION AND RATIONALE

Patients with deep dermal burns or full thickness wounds always require a surgical reconstruction with skin grafts to restore the integrity of the outer skin layer. Most of the deep burn wounds are covered with split thickness skin grafts (SSG) which is the standard of care (SOC) treatment nowadays. However, in order to achieve rapid wound closure in extensively burned patients, the shortage of available donor areas for skin graft harvesting represents a significant problem. As a result, coverage of the majority of burn wounds or full-thickness skin defects unavoidably requires an expansion of the skin graft before application.

Currently there are two distinct methods for skin graft expansion. The most frequently used technique worldwide is the easy and fast meshed graft technique whereby the skin theoretically can be enlarged 1.5 to 9 times. The larger the expansion rate, the less donor skin is needed. Unfortunately, it has been demonstrated that in reality the claimed expansion ratios are never achieved with meshed grafts whereby e.g. a 1:3 expansion only results in about 60% increase in size. Therefore, even more donor skin or even larger expansion ratios are needed in order to cover all wounds in severely burned patients. Various additional problems arise due to the use of widely meshed skin grafts, both for the patient and for the surgeon. Mesh-expanded skin grafts take much longer to completely epithelialize and often result in hypertrophic scar formation and contractures. Moreover, in the long-term, a lasting “fishnet or string-vest” pattern will always be visible in meshed grafted areas. An additional technical problem is that skin grafts that are meshed with a ratio above 1:3 are fragile and very difficult to handle for the surgeon.

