#### 6.4 Summary of known and potential risks and benefits

Meshed grafts: This technique for skin expansion and grafting is most widely performed, seen it is a very user-friendly and fast procedure. However, mesh grafting also has its shortcomings. Theoretically an expansion ratio from 1:1.5 until 1:9 are possible In practice, meshed grafts do not expand as much as suggested. Expansion ratios of 1:1,5 and 1:3 turned out to give an surface area expansion of 1,36x and 1,80x respectively Moreover, an expansion ratio above 1:3 is very fragile and therefore difficult to properly cover and fixate on wounds. Besides, the 'fish-net' pattern of the meshed graft remains visible in the long-term scar. For this reason, meshed grafts do not fall within the preferred skin expansion and grafting techniques for extensive wounds with limited donorsite.

Micrografting: True expansion ratios up to 1:9 are achieved, which leads to a smaller donorsite. In comparison with meshed grafts, micrografting will not give fragility problems with a large expansion ratio. Also small graft fragment can be used, in contrast with meshed grafts were only long strips of graft can be utilized (4). Therefore is a preferable technique for especially extensive wounds (2). Graft failure due to bacterial infection is limited to failure of a few islands instead of the whole graft, because of all separate gauzes. Moreover, in our experience the scar quality of micrografts showed to be very good and might even better

than the scars of meshed grafts. Drawbacks of micrografting are mainly based on a more labour-intensive and time-consuming procedure compared with meshed grafts.

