## 8. METHODS

### 8.1 Study parameters/endpoints

#### 8.1.1 Main study parameter/endpoint

- Long-term scar quality 12 months after skin transplantation assessed with the Patient and Observer Scar Assessment Scale (POSAS).

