#### 8.1.2 Secondary study parameters/endpoints (if applicable)

- Long-term scar quality 3 and 12 months after skin transplantation
  - Subjective measurement of scar quality with Patient and Observer Scar Assessment Scale (POSAS). This is based on multiple aspects of scar formation such as: vascularization, pigmentation, texture, thickness, pliability, itch and pain, and is performed by member of research team and by patient.
  - Objective measurements of scar color and pigmentation with the Mexameter or Dermaspectrometer. Skin elasticity is objectively measured with the Cutometer.
- Skin graft technique preferred by patient
  - Patient gives overall indication as to what skin graft technique he/she would prefer if he/she were to require skin grafting again: weekly during admission, and at 3 and 12 months follow up
- Donorsite size and ratio of donorsite size and actual graft size (cm^2)
  - Surface areas will be calculated with a 3D-camera (Woundworks inSight)
- Take rate of skin grafts
  - Take rate will be clinically assessed at 8 +/- 2 days and expressed as the percentage of micrografted and meshed graft take
- Healing time
  - Clinical assessment of wound healing 14 and 21 days +/- 2 post application expressed as percentage of the total wound surface area healed
  - Time to complete wound closure where complete wound closure is defined as > 95% re-epithelialization of the wound with the absence of drainage and no longer needing a substantial wound dressing
- Bacterial load
  - Wound swabs for semi-quantitative investigation
  - Semi-quantitative bacteriology in both groups
  - Percentage of patients within both groups with clinical wound infection requiring systemic antimicrobial therapy
  - 'Clinical infection' is defined as the presence of cellulitis and/or visible purulence and/or lymphangitis combined with one or more of the following: local wound pain/erythema/edema/malodor

- Pain
  - Will be evaluated in the autografted target wounds with help of a Visual Analogue Scale (VAS score) on day 2 post surgery, before and after removal of Surfasoft®/Urgotul in case of meshed skin grafts or plissees in case of micrografting, and thereafter once weekly during the hospitalization period. After hospital discharge pain will be evaluated again at the 3 and 12 months follow ups
- Number of secondary procedures
  - Re-interventions in study areas due to insufficient take or necessity of reconstructive surgery
- Mobility at 3 and 12 months

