## Follow-up

### Measurements 3 and 12 months after operation

- Regular check-up after hospital discharge
- Preference skin grafting technique
  - Question preference of patient regarding skin grafting technique on this moment
- Scar quality:
  - Patient and Observer Scar Assessment Scale
  - Scar color and pigmentation measurement with Mexameter or Dermaspectrometer
  - Scar elasticity measurement with Cutometer
- Mobility
  - Questionnaire - Quick Disabilities of the Arm, Shoulder and Hand (Quick DASH) - for (burn)wounds concerning upper extremity
  - Questionnaire - Lower Extremity Functional Scale (LEFS) - for (burn)wounds concerning lower extremity
  - Objective measurement of range of motion with a goniometer
- Quality of life
  - Questionnaire - EQ5D-5L
  - Questionnaire - Short Form Health Survey 36-item (SF36)
  - Questionnaire - Dermatology Life Quality Index (DLQI)

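### Assessor blinding of the 12-month observer POSAS is stated as fact, although the protocol says elsewhere that the mesh pattern stays visible in the scar

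*Protocol*

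**What the plan says.** Section 8.2 concedes that the surgeon cannot be blinded, then says of the follow-up: "Outcome assessment will be blinded as the junior investigator/research nurse who does the follow-up measurements is unaware of the technique used". The only basis given is that the assessor does not know which technique went to which of the two labelled areas. No step is described to keep that knowledge from arising at the examination.

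The protocol describes the meshed scar in three places:
- Section 1, on the fishnet or string-vest appearance: the "pattern will always be visible in meshed grafted areas".
- Section 6.4: the fishnet "pattern of the meshed graft remains visible in the long-term scar".
- Summary: the "pattern often stays visible in the eventual scar".

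The primary endpoint is the POSAS at 12 months (section 8.1.1), and section 10.1 analyses its observer score. Section 8.1.2 classes the POSAS as a subjective measurement, includes texture among the aspects rated, and has it scored by a member of the research team and by the patient.

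At the same visits patients are asked about technique. Section 8.1.2 has it that the "Patient gives overall indication as to what skin graft technique he/she would prefer if he/she were to require skin grafting again". This is asked each week in hospital and at both follow-up visits. The follow-up list in section 8.3 includes "Question preference of patient regarding skin grafting technique on this moment", placed above the POSAS.

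**The concern.** Section 8.2 treats an assessor who has not been told the allocation as an assessor who does not know it. By the protocol's own account the meshed scar carries a recognisable mark, and the assessor's task is to look closely at the scars. With one area of each type per patient, identifying the mesh settles both.

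The primary outcome is a rating, so knowledge of the technique can move it. Section 1 states the hypothesis that micrografting gives the better scar and reports favourable experience with it in the authors' own centre. If a rater shares that expectation, the resulting shift tends to fall on the same side in each pair. Within-patient pairing removes differences between patients but not a shift of this kind, and more patients would only make it easier to declare significant.

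A visible mesh pattern that earns a worse texture score on its merits is a real difference in scar quality, not bias. What is at stake is the additional part that comes from expectation. Readers of the results would also be told that this part had been excluded by blinding.

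**Working it through.** **The statements set against each other**

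1. Section 8.2: the assessor does not know the technique in A or B.
2. Sections 1 and 6.4: the mesh pattern is lasting and visible, stated without qualification. Summary: it is visible often.
3. Section 8.2: each patient contributes one area of each technique, either two wounds or two halves of one wound.
4. From 2 and 3, an assessor who sees the pattern in one area knows the technique in both. Statement 1 then fails for that patient. On the wording of sections 1 and 6.4 this happens generally; on the wording of the Summary it happens often. On neither reading can blinding be asserted flatly.

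**The plan's own figure (section 4.4)**

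Inputs: mean difference 1, SD 2.4, correlation 0.5, two-sided alpha 0.05.

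- SD of the paired difference = √(2 × 2.4² × (1 − 0.5)) = √5.76 = 2.4.
- Noncentrality at 63 pairs = 1 × √63 / 2.4 = 3.31, with 62 degrees of freedom.
- Exact power from the noncentral t is 0.902 at 63 pairs and 0.807 at 48 pairs. Both match the table.
- Dropout: 63 / (1 − 0.10) = 70, as stated.

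**Illustration of what a rater shift would do**

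Suppose the true difference is 0 and knowledge of the technique moves the mean paired difference by *b* points. The values of *b* are assumptions; the documents give none. The chance that the planned paired t-test rejects is the same power formula with *b* in place of the mean difference, so noncentrality = *b* × √63 / 2.4 = 3.307 × *b*.

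| Assumed shift *b* (points) | Noncentrality | Chance of rejecting |
|---|---|---|
| 0 | 0 | 0.05 |
| 0.10 | 0.33 | 0.06 |
| 0.25 | 0.83 | 0.13 |
| 0.50 | 1.65 | 0.37 |
| 0.75 | 2.48 | 0.69 |
| 1.00 | 3.31 | 0.90 |

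A shift of half the planned effect gives 0.37 / 0.05 = 7.4 times the nominal error rate. The table shows sensitivity only; it does not estimate the bias in this trial. No revised sample size follows from it, because bias is not a matter of numbers.

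**The case against.** The best case for the protocol is that not telling the assessor and labelling the areas A and B are reasonable measures, and that some recognition is unavoidable when these two techniques are compared. The sentence in section 1 also comes within a discussion of widely meshed grafts, whereas section 5.1 uses 1:2 and 1:3, and the Summary says only that the pattern is often visible. This has weight: complete failure of masking in every patient is not shown. The contradiction remains, because the sentence in section 1 refers to meshed areas in general, section 6.4 is equally general, and even frequent recognition is incompatible with an unqualified statement of blinding.

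A reader might infer more than the text supports:

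- **That the preference question reveals the allocation to the assessor before scoring.** The protocol does not say who asks it, does not say that the order of the list is the order of the visit, and does not say that the answer links a technique to an area. Section 8.2 speaks of the person who does the follow-up measurements, and section 8.3 lists the question under measurements. The same person asking it is therefore plausible, but no more than that.
- **That the patient's own POSAS breaks the blinding claim.** Section 8.2 does not claim that patients are blinded, and section 10.1 analyses the observer score.
- **That the two scars are scored next to each other.** Section 8.2 prefers two separate wounds and divides one wound only as an alternative.
- **That the assessors are known to favour micrografting.** The favourable experience is the authors', reported for one centre. Nothing is said about the views of the junior investigator or research nurse who scores.
- **That the false-positive rate will be 13% to 69%.** Those figures depend entirely on assumed shifts.

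**Conclusion.** The point holds as a contradiction within the protocol. Section 8.2 asserts a blinded outcome assessment that sections 1 and 6.4, and more mildly the Summary, make unlikely in many patients. It concerns the primary endpoint, which is subjective and observer-rated. The visible pattern is enough to support this; the preference question is only a possible further route that is easy to close.

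The size of any resulting bias cannot be derived from the documents. It depends on how often the pattern is recognised at 1:2 and 1:3, and on whether recognition changes the rating, neither of which is given. Under the assumed shifts, a quarter of a point would raise the error rate from 5% to about 13%, and half a point to about 37%. The test, the sample size and the choice of endpoint are not affected by this point.

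**What to change.** 1. In section 8.2, replace the sentence on blinded outcome assessment by: *Assessors are not told the allocation; masking may not hold because the mesh pattern can be visible.* Do not describe the primary outcome as assessor-blinded in the protocol or in reports.
2. In sections 8.1.2 and 8.3, place the preference question after all scar scoring at the 3- and 12-month visits, and word it as area A or area B.
3. Have the assessor record straight after scoring which area is thought to be mesh, and report the proportion correct as a description of masking. With two areas, one of each type, pure guessing gives 1/2. Do not stratify POSAS by guess: a correct guess is related to how different the scars look, and therefore to the outcome itself.
4. State that a POSAS difference will be interpreted with this limitation and alongside the Cutometer and Mexameter or Dermaspectrometer results, which are already planned at the same visits.

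The cost is wording, one item on the case report form and a changed order at the visit, with no extra staff or visits. The trial gives up the claim of assessor blinding. These steps disclose and measure unmasking; they do not prevent it, so any rater bias would remain in the POSAS result.
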